## 30. Power calculations and sample size determination

### 30.1. Primary combined clinical endpoint

The primary combined endpoint will be cardiac death and HHF at 12 months. These endpoints have been selected as they are the most relevant clinical endpoints that are likely to be affected by RIC, an intervention which protects cardiomyocytes against acute IRI. According to the UK NIAP 2008 database, cardiac mortality at 12 months ranged from 5.8%-16.7% depending on the call to balloon time, with the overall 12 month death rate of 8.7% for all PPCI patients. In a recent Danish clinical study post-PPCI, the one year mortality was 9.4% and the cumulative risk of readmission with heart failure was 8%. In another, non-UK based, clinical study, the incidence of HHF was 12.7% at 12 months post-PPCI. We have based our power calculations on these published studies, accounting for the marked improvements in clinical outcomes in the contemporary era by using much more conservative event rates.

As a conservative estimate we will use a combined cardiac death and HHF event rate of 8.5% at 12 months for all-comer STEMI patients. In the combined ERIC-PPCI / CONDI 2 trial we estimate the effect size to be a 25% relative reduction in the event rate. The rationale for this is based on proof-of-concept clinical studies in which RIC, and related therapeutic interventions such as ischaemic postconditioning, have reported 40-50% reductions in MI size. To demonstrate a 25% reduction in the primary composite endpoint in the RIC-treated group (from 8.5% to 6.4%), with 80% power and at the 5% significance level, will require 2395 patients per treatment arm which equates to 4790 patients in total. Therefore, we will need to recruit 5400 STEMI patients (allowing for a 10% drop out rate at 12 months) between UK and Denmark (2800 STEMI patients in the UK and 2600 STEMI patients in Denmark). In the ERIC-PPCI trial we intend to recruit 2800 STEMI patients in the UK through 30 PPCI sites.

If the event rate in the control arm is higher than the estimated 8.5% or the losses less than 10% then the power will increase. The ERIC-PPCI UK arm of the trial of 2800 patients alone would provide in excess of 80% power to detect a relative reduction of 35% from 8.5% to 5.5% allowing for 10% losses to follow up.

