## 33. Randomisation

### 33.1. Randomisation procedure

Patients will be randomised to either RIC or sham RIC by a designated research investigator, this investigator will therefore be unblinded to treatment allocation. Randomisation will be coordinated centrally by the LSHTM CTU via a secure website [www.sealedenvelope.com](http://www.sealedenvelope.com) and will be stratified by centre using random permuted blocks.

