**SOP for Procedure-related AMI report in Condi 2 (not part of secondary outcome measures)**

Validation categories: Yes or No

[figure not shown]

\*Modified from: "Third universal classification of myocardial infarction". European Heart Journal (2012) 33, 2251-2567 and "2014ACC/AHA Key Data Elements and Definitions for Cardiovascular Endpoint Events in Clinical Trial". Circulation.2015;132:302-361

- **S/T methodology and associated work plan**

- **Trial Design:**

Multinational investigator-driven, multi-centre, randomised, controlled, single-blind (Outcomes Assessor), parallel assignment, prospective clinical efficacy trial to investigate whether RIC can improve clinical outcomes (cardiac mortality and HHF) at one year in STEMI patients undergoing pPCI.

- **Setting**

In all 5700, STEMI patients will be included.

Four centres with on-site facilities for pPCI in Denmark will recruit app. 1,800 STEMI patients in total over a 36-month period.

Centres in Asturias, Spain, and Belgrade, Serbia will recruit app. 800 STEMI patients in total over a 36-month period.

An aligned sister study in the ERICCA-collaboration (ERIC-pPCI) including 30 primary PCI centres in the UK will include 3,000 patients.

Data collection and analysis will be undertaken through the Department of Cardiology and Department of Clinical Epidemiology, Aarhus University Hospital Skejby Clinical Trials Unit.

- **Target population**

Possible study candidates are patients with putative STEMI acute admitted to one of the heart centres. There will be no advertising for patients. A total of 5,700 patients are to be included over a 36 months period.

| Inclusion criteria for recruitment                                                                                                                                                        | Exclusion criteria for recruitment        |
|--------------------------------------------------------------------------------------------------------------------------------------------------------------------------------------------------|--------------------------------------------------|
| Male and female patients (>18 years old) presenting with chest pain for more than 30 minutes                                                                                                     | Previous by-pass surgery                         |

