The admitting ambulance doctor, the doctor at the receiving hospital, or the paramedic will orally inform the patient based on the short written information (B) and hand out the written informations (A+B). After oral and written informed consents are obtained the patient will sign the agreement form and be randomised via a secure web site to pPCI with or without RIC by the doctor on duty at one of the receiving hospitals. Computer-generated blocked randomisation lists, stratified by centre, will be prepared in advance of the study.

After information is given in the acute phase, the patient does not have much time for reflection before signing the informed consent form. Therefore, a study nurse will give the patient additional oral information after the acute phase by or the doctor performing the pPCI based on the full written information (A). Both during the first and second stage of information it will be emphasised that the patient has the right to withdraw his/her informed consent at any time.

- **Procedures and treatment**

*Control group:* Will be treated according to standard procedures in the ambulance.

*Intervention group, RIC group:* The CellAegis auto RIC (automated blood pressure cuff) will be placed on the upper arm and inflated to 200mmHg for 5 minutes and then deflated for 5 minutes, a programmed cycle which is repeated 4 times in total (therefore the total length of the RIC protocol is 40 minutes). If the initial systolic blood pressure is >175mmHg, a manual cuff will be used to and inflated to 25mmHg above the systolic blood pressure. In recruiting centres where randomisation occurs at the hospital or in cases with short transportation time, the RIC protocol will continue during PCI until successful or until immediately before reperfusion.

Further, the patients will be treated according to standard procedures in the ambulance.

|                                                    | Acute intervention |         | Index event    | Follow up |
|----------------------------------------------------|--------------------|---------|----------------|-----------|
| Randomisation                                      | Intervention       | Control |                |           |
| Blood samples                          |                    |         | X              |           |
| e-CRF                                  |                    |         | X              | X         |

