## ● ANALYSIS POPULATIONS

### ○ Definition of Populations for Analysis

The primary analysis will be performed on an intention to treat basis, by including all patients where possible according to the group to which they were randomised irrespective of whether they received the intervention as allocated. A secondary per protocol analysis will be undertaken including only patients who receive the allocated intervention as intended.

- Intent-to-treat (ITT)

The intent-to-treat analysis population will include all patients randomised to CONDI-2 and ERIC-PPCI regardless of whether they received their randomised intervention as specified (i.e. including all patients whether or not all cycles of RIC or sham RIC were fully completed according to protocol and whether or not the patient received PPCI).

- Per Protocol (PP)

The per protocol analysis population will include confirmed STEMI patients randomised to CONDI-2 and ERIC-PPCI who received their randomised intervention as specified (i.e. including patients where all four cycles of RIC or sham RIC were fully completed according to protocol and the patient received PPCI).

- STATISTICAL ANALYSIS

- General

The final combined statistical analysis will be performed as pre-specified in this SAP. Any, additional, post-hoc, exploratory analyses completed to support these planned analyses which are presented in the trial reports but not included in this SAP, will be clearly identified as such. Analyses will be stratified by trial (i.e. CONDI-2 or ERIC-PPCI) where indicated below.

- Methods for Handling Missing Data

For the outcomes considered in this analysis, missing data are expected to be minimal. However, multiple imputation methods may be used depending on the scale and pattern of the missing data.

- Analysis of Primary Endpoint – cardiac death and hospitalisation for heart failure 12 months after randomisation.

The primary combined endpoint is defined as the first occurrence of HHF or cardiac death within 12 months of randomisation. The primary analysis will be a comparison of the rate of the first occurrence of cardiac death or HHF between the RIC and control arms of the trial. Hazard ratios and 95% confidence intervals will be calculated using Cox proportional hazards modelling, stratified by trial,

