#### ○ Subgroup analysis

A limited number of pre-specified subgroup analyses are planned on the primary outcome. These will be limited to age, diabetic status, LAD vs non-LAD STEMI, TIMI flow (0-1 and 2-3) pre-angioplasty and time of first medical contact to PPCI (i.e. balloon time). The subgroups will be analysed by inclusion of an interaction term between treatment group and the subgroup in the Cox regression model.

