#### ○ Cardiac Biomarkers Substudy

Values of high-sensitivity troponin T will be converted into a 48 hour area under the curve (AUC) summary measure for analysis. Differences in the mean AUC together with 95% confidence intervals will be calculated using a linear regression model. Troponin T will be collected at admission and 6-8, 24, and 48-72 hours post-PPCI in CONDI-2, and at admission and 6, 12, 24 and 48 hours post-PPCI in ERIC-PPCI. Where necessary, multiple imputation by chained equations will be used to account for missing information. Separate imputation models will be used for each trial. In CONDI-2, the troponin T measurement at 48-72 hours post-PPCI will be split in to those occurring at 48 hours (between 36 and 60 hours after the admission measurement) and those occurring at 72 hours (between 60 and 84 hours after the admission measurement) before multiple

imputation on all measurements up to 72 hours post-PPCI is performed. In ERIC-PPCI, multiple imputation on all measurements up to 48 hours post-PPCI will be performed. Twenty imputed datasets will be generated separately for each trial before being combined. The estimated difference in mean 48 hour AUC between the two treatment groups will be calculated using Rubin's rules. The distribution of the outcome variable will be investigated for non-normality and if necessary a data transformation will be made or a non-parametric statistical analysis will be conducted.

The following variables will be included in the multiple imputation models: troponin-T at each time point; treatment group; country (CONDI-2 only); gender; baseline age, diabetes, hypertension, systolic blood pressure, Killip class, and body weight; use of aspirin,  $\beta$ -blockers, nitrates, diuretics, Clopidogrel, Ticagrelor/Brillique, and metformin at admission for PPCI; previous myocardial infarction; peripheral vascular disease and hypercholesterolaemia at admission for PPCI; call to balloon time; pre/peri-procedural use of nitrates; length of index hospitalisation; and cardiac death within 12 months.

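### The primary Cox model is valid but adjusts only for trial; pre-specifying a few baseline covariates would be a cheap gain in power, and centre strata would not.

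*Supplement*

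**What the plan says.** SAP version 3, 5.3 (Analysis of Primary Endpoint) takes time to first cardiac death or HHF within 12 months: "Hazard ratios and 95% confidence intervals will be calculated using Cox proportional hazards modelling, stratified by trial". The one-year risk difference is stratified the same way. The General paragraph (5.1) sets the rule: "Analyses will be stratified by trial (i.e. CONDI-2 or ERIC-PPCI) where indicated below". Neither centre nor any baseline covariate appears in the primary analysis.

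Randomisation is finer than this. In ERIC-PPCI version 5.0 (33.1) it "will be stratified by centre using random permuted blocks". CONDI-2 version 10 (Patient information) states: "Computer-generated blocked randomisation lists, stratified by centre, will be prepared in advance of the study".

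Baseline predictors are available, at least in part:

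- Subgroup analysis of the primary outcome (SAP 5.5): "These will be limited to age, diabetic status, LAD vs non-LAD STEMI, TIMI flow (0-1 and 2-3) pre-angioplasty", plus time from first medical contact to PPCI.
- ERIC-PPCI CRF (36.2): diabetes, previous MI, blood pressure and Killip class, among others.
- Imputation models for the biomarker substudy (SAP 5.6): "baseline age, diabetes, hypertension, systolic blood pressure, Killip class, and body weight", with previous MI named further on. Only country is marked as specific to one trial.

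**The concern.** A time-to-event comparison that leaves out strong predictors estimates a hazard ratio averaged over patients of very different risk. That average lies closer to 1 than the ratio between like patients, so the test loses some power. If the predictors are recorded anyway, the loss can be avoided without recruiting anyone.

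The design has little slack. The assumed control rate in ERIC-PPCI has already fallen from 11.0% (version 1.0) to 8.5% (version 5.0), and CONDI-2 version 10 assumes 8.0%. The SAP also requires analyses that it does not list to be labelled as such, so an adjusted primary result added later could only be presented as post hoc.

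**Working it through.** **1. The plan's own figure.** Inputs (SAP 2.3): control 8.5%, a 25% reduction (6.375%, printed as 6.4%), 80% power, 5% significance taken as two-sided, equal arms.

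n per arm = [1.960·√(2p̄(1−p̄)) + 0.842·√(p₁(1−p₁) + p₂(1−p₂))]² / (p₁ − p₂)²

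With p₁ = 0.085, p₂ = 0.06375 and p̄ = 0.074375 this gives 2,393; with p₂ = 0.064 it gives 2,454. The stated 2,395 is reproduced. It is an unadjusted calculation, so the stated 80% does not depend on covariates.

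**2. Slack.** 4,790 / 0.90 = 5,323 to recruit, against 5,400 planned. Evaluable: 5,400 × 0.90 = 4,860, and 4,860 / 4,790 = 1.015, so about 1.5% spare. At the 8% versus 6% of CONDI-2 version 10, the same 4,860 patients give about 78% power.

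**3. Power of the planned Cox model.** HR = ln(1 − 0.06375) / ln(1 − 0.085) = 0.742. Events needed: 4 × (1.960 + 0.842)² / (ln 0.742)² ≈ 352. Expected: 4,860 × (0.085 + 0.06375) / 2 ≈ 361. Power is about 81%.

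**4. Effect of adjustment, by simulation.** There were 2,500 trials per scenario, each with 4,860 patients. ERIC-PPCI had 2,800 × 0.9 = 2,520 patients in 30 centres ("we intend to recruit 2800 STEMI patients in the UK through 30 PPCI sites"). CONDI-2 had 2,600 × 0.9 = 2,340 patients in 6 centres: "Four centres with on-site facilities for pPCI in Denmark will recruit app. 1,800 STEMI patients", plus an assumed two in Spain and Serbia. Blocks of 4 are assumed. The overall 12-month rates were held at 8.5% and 6.375% throughout, which is the effect the plan is sized for. A single baseline score stands for the covariates. Its strength and the between-centre SD (0.2 on the log hazard in this table) are assumptions.

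| AUC of baseline score | Trial strata (planned) | Trial strata + score | Gain (points) | Centre strata + score |
|---|---|---|---|---|
| 0.64 | 81.4% | 81.9% | 0.5 | 81.6% |
| 0.72 | 79.7% | 82.1% | 2.4 | 81.8% |
| 0.76 | 80.6% | 84.3% | 3.7 | 84.2% |
| 0.80 | 79.2% | 86.7% | about 7.6 | 86.4% |

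Each power figure has a Monte Carlo standard error of about √(0.8 × 0.2 / 2,500) = 0.8 points. The models in a row were fitted to the same simulated trials, so the gains are steadier than the levels.

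**5. Where the gain comes from.** At AUC 0.76 the average hazard ratio moves from 0.740 to 0.728, while the standard error stays at 0.107. The test statistic goes from 0.301 / 0.1069 = 2.82 to 0.317 / 0.1069 = 2.97. The estimate moves; the precision does not.

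**6. Centre alone.** With no covariates, replacing trial strata by centre strata moves power from 80.3% to 80.5% (centre SD 0.2) and from 80.6% to 81.0% (centre SD 0.5).

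**7. Validity.** With no treatment effect, a score of AUC 0.76 and centre SD 0.5, the planned model rejects in 4.96% of trials.

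**The case against.** The strongest reply is that nothing in the plan is broken. The sample size is an unadjusted calculation that reproduces, type I error is held, and the Cox approach follows the ERIC-PPCI protocol (41.2). The unadjusted model needs no harmonised covariates and no rule for missing baseline values. It also keeps a marginal hazard ratio beside the planned risk differences. All of that stands, so leaving covariates out does save something.

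Availability is also not fully shown. The imputation list serves the biomarker substudy, and CONDI-2 troponin comes from a subset of sites. CONDI-2 version 10 shows no CRF list confirming Killip class or previous MI for every patient. The separate trial SAPs and the parallel data document are not among the documents, and could contain adjusted analyses. This limits which covariates can be named now. It does not touch age and diabetes, which the primary-outcome subgroups already require.

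Three stronger readings are tempting, and the documents do not support them:

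- **The planned analysis falls short of 80%.** Fixing the hazard ratio at 0.745 within covariate levels and then adding heterogeneity gives about 75% or less. But that shrinks the overall effect: the RIC rate becomes 6.51% or 6.61%, depending on the spread assumed, instead of 6.375%. At the plan's own rates the power is about 80%.
- **Omitting the centre strata costs power or validity.** Steps 6 and 7 show neither.
- **The unadjusted hazard ratio is biased.** Its distance from the adjusted one reflects two different quantities, marginal and conditional, not an error in either.

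**Conclusion.** The point holds as a missed, inexpensive efficiency gain and a missing pre-specified adjusted analysis. It is not a flaw in validity or in the stated power. The likely size is 2 to 4 points of power if the covariates together reach an AUC of 0.72 to 0.76, and up to 7 to 8 points at 0.80. At 0.64 the gain is negligible. The result rests on assumed predictor strength, assumed centre variation and complete baseline data; the documents supply none of these. The case for acting is that the margin is only about 1.5% and that CONDI-2 version 10 itself assumes a lower event rate. The benefit comes from the covariates alone, so there is no power argument for making centre a stratum of the primary model.

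**What to change.** Before unblinding, amend SAP 5.3 as follows:

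- Make the primary model a Cox model stratified by trial and adjusted for a short fixed list common to both trials. Age and diabetes go in now. Add Killip class, systolic blood pressure and previous MI once they are confirmed as collected for all CONDI-2 patients.
- Fix the form of each covariate and a simple rule for missing baseline values.
- Report the unadjusted trial-stratified hazard ratio as a sensitivity analysis, and a centre-stratified or centre-frailty model as another.
- State that the primary hazard ratio is conditional on the covariates. The planned one-year risk differences can stay as the marginal summary.

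The cost is SAP wording, harmonising a few variables across two CRFs, and a hazard ratio that is conditional instead of marginal. If treatment codes have already been released, the adjusted model should be reported only as post hoc, as SAP 5.1 requires.

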## ○ Secondary Objectives

To determine the effects of RIC on:

- Rates of the individual components of the primary endpoint at 12 months
- Rates of the combined endpoint as well the individual components of cardiac death and/or HHF at 30 days.
- Rates of the individual endpoints of all-cause death, repeat coronary revascularisation, reinfarction, stroke at 30 days and 12 months.

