and Kaplan-Meier curves will be produced. The time scale used for survival analysis will be time to the primary endpoint since randomisation. Participants will be censored if they die of a non-cardiac cause, are lost to follow-up, withdraw from the study, or at 12 months after randomisation. The assumptions underlying the Cox model will be assessed and if there is clear non-proportionality hazard ratios will be presented separately for the relevant time periods.

In addition risk differences at one year, again stratified by trial, will also be calculated together with 95% confidence intervals.

- **Analysis of Secondary, and Other Efficacy Endpoints**

- Cardiac death and HHF at 30 days**

The RIC and control arms of the trial year will be compared on rate of the first occurrence of cardiac death or HHF up to 30 days following randomisation. Hazard ratios and 95% confidence intervals will be calculated using Cox proportional hazards modelling, stratified by trial, and Kaplan-Meier curves will be produced. The time scale for analysis will be time since randomisation. Participants will be censored if they die, are lost to follow-up, withdraw from the study, or at 30 days after randomisation. The risk difference stratified by trial together with 95% confidence intervals will also be calculated.

- Individual components of cardiac death and HHF at 30 days and 12 months**

Survival analysis will be used to examine the individual components of the composite outcome, using the same methods as outlined above.

- All cause death, repeat coronary revascularisation, reinfarction, stroke at 30 days and 12 months**

Survival analysis will be used to examine each of these clinical outcomes and MACCE (all-cause death, repeat coronary revascularisation, reinfarction, or stroke) using the same methods as outlined above.

- Repeat HHF and cardiac death**

In order to take account of recurrent HHF in patients while also accounting for the competing mortality, a parametric joint frailty model will be used for

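### SAP v3, 5.4.1: the 30-day censoring rule contradicts its own endpoint, and neither rule that 5.4.2 and 5.4.3 could inherit fits all-cause death or MACCE

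*Supplement*

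**What the plan says.** All references are to SAP v3.

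- **5.3, 12-month primary endpoint.** The event is the first HHF or cardiac death. The censoring rule is "Participants will be censored if they die of a non-cardiac cause"; the other reasons given are loss to follow-up, withdrawal and reaching 12 months.
- **5.4.1, 30-day composite.** The arms are "compared on rate of the first occurrence of cardiac death or HHF up to 30 days following randomisation". The censoring rule is "Participants will be censored if they die, are lost to follow-up, withdraw from the study, or at 30 days after randomisation".
- **5.4.2, individual components, both time points.** The whole instruction is: "Survival analysis will be used to examine the individual components of the composite outcome, using the same methods as outlined above".
- **5.4.3, all-cause death, revascularisation, reinfarction and stroke, both time points.** These outcomes are analysed together with "MACCE (all-cause death, repeat coronary revascularisation, reinfarction, or stroke) using the same methods as outlined above". The section has no event or censoring rule of its own.
- **2.2, secondary objectives.** These include "Rates of the individual endpoints of all-cause death, repeat coronary revascularisation, reinfarction, stroke at 30 days and 12 months".

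The statistical sections of the ERIC-PPCI protocol v5.0 and the CONDI-2 protocol v10 call for survival analysis of these outcomes. They give no censoring rules that would settle the matter.

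**The concern.** In 5.4.1 a cardiac death before any HHF is an event by the endpoint definition and a censoring time by the censoring sentence. It cannot be both. If the censoring sentence is followed, the 30-day composite becomes time to first HHF, and it no longer answers the stated secondary objective.

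The problem spreads through the back-references. All-cause death and MACCE contain deaths from every cause, but both rules that precede them in the SAP censor at least some deaths. A programmer who takes either rule literally will get these analyses wrong.

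The wording matters because section 5.1 commits to running the combined analysis as pre-specified and to labelling anything else post hoc. The Introduction gives the work to statisticians from both trials. A rule that must be silently reinterpreted can be read differently by each team, and the choice is left open until the data are in hand.

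**Working it through.** **1. The plan's own figure.** The SAP states a sample size for the 12-month primary endpoint only (section 2.3). The formula, with pooled variance, two-sided 5% (sidedness is not stated, so this is assumed) and 80% power, is

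n per arm = [z(0.975)·√(2p̄(1−p̄)) + z(0.80)·√(p₁(1−p₁) + p₂(1−p₂))]² / (p₁−p₂)².

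- With p₁ = 0.085 and p₂ = 0.75 × 0.085 = 0.06375, n = 2393. The SAP states 2395.
- With the rounded 6.4%, n = 2454, which is still within 3%.
- Dropout: 4790 / 0.90 gives 5323, against 5400 planned.

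The figure reproduces. No 30-day quantity enters it, so the sample size is untouched.

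**2. The two rules side by side.** Section 5.3 says "Participants will be censored if they die of a non-cardiac cause". Section 5.4.1 drops the qualifier and censors at any death. Loss to follow-up, withdrawal and an administrative cut-off appear in both rules, so the cause restriction is the only difference apart from the horizon.

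**3. Each rule applied to each endpoint.**

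| Endpoint | Intended event | 30-day rule (5.4.1) taken literally | 12-month rule (5.3) taken literally |
|---|---|---|---|
| 30-day composite | first cardiac death or HHF | first HHF only | correct, if adopted with a 30-day cut-off |
| Cardiac death alone | cardiac death | no events | correct |
| All-cause death | any death | no events | cardiac deaths only |
| MACCE | any death, revascularisation, reinfarction or stroke | non-fatal components only | non-cardiac deaths lost |
| HHF, revascularisation, reinfarction or stroke, each alone | the non-fatal event | correct for a cause-specific hazard ratio | cardiac death is not on the censoring list, so its handling is unstated |

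No single column is right for every row. For all-cause death and MACCE both columns are wrong, so the defect there does not depend on which rule the back-reference means.

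**4. Size, on assumptions only.** No 30-day rate is given in the documents. Assume 2700 per arm, a control 30-day composite rate of 4-6%, a rate ratio of 0.75, and 20-50% of first events being cardiac deaths without earlier HHF.

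- Events if cardiac deaths count: 2700 × 0.04 × 1.75 = 189, up to 2700 × 0.06 × 1.75 = 284.
- Events lost: from 0.20 × 189 = 38 to 0.50 × 284 = 142.
- Events left: from 0.50 × 189, about 94, to 0.80 × 284 = 227.
- Power by Schoenfeld's approximation, Φ(√E/2 × |ln 0.75| − 1.96): 51-68% if cardiac deaths count, and 29-58% under the literal rule.

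The power comparison assumes the same hazard ratio for both components. It shows lost precision only, because the literal rule also changes what is estimated.

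As a plausibility bound, the SAP's planning rates imply 5400 × (8.5% + 6.4%)/2 = 5400 × 7.45%, about 402 first events over the whole 12 months. The assumed 189-284 by day 30 fit within that.

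**The case against.** The strongest reply is that the intent is clear. The paragraph names cardiac death as part of the endpoint, and censoring ordinarily applies to patients who have not had the event. A competent analyst would count the cardiac deaths. This stands as far as intent goes: the text is contradictory, and nothing shows a plan to discard cardiac deaths. It does not rescue the wording, because 5.3 shows that the authors had the correct qualifier available.

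It can also be said that the back-references must be adapted to each endpoint, since a rule that stops at 30 days cannot govern a 12-month analysis. That is fair. A reader might infer that all-cause and cardiac death lose every event, but this is only one reading. Under the 5.3 rule the cardiac-death component is correct. What survives is that all-cause death and MACCE are mis-specified under either rule.

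A reader might further infer that any early mortality effect would go unseen. The documents do not support that. The 12-month primary analysis runs from randomisation and counts every first-event cardiac death from day 0. The joint frailty model in 5.4.4 also gives a separate hazard ratio for cardiac death.

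Finally, one might ask for competing-risk curves for the non-fatal endpoints. That is a separate matter. Censoring at death is right for a cause-specific hazard ratio, the SAP does not say that its risk differences come from Kaplan-Meier estimates, and 5.3 itself censors a competing event (non-cardiac death). The present error does not depend on it.

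**Conclusion.** The point holds as a wording error that gives a wrong result if followed. In 5.4.1 the censoring sentence contradicts both the endpoint definition and 5.3. Taken literally, it removes cardiac deaths without earlier HHF from the 30-day composite. In 5.4.2 and 5.4.3 the inherited rule is unidentified, and for all-cause death and MACCE neither candidate is correct. That part rests on the text alone and needs no assumption about rates.

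The number of events at stake cannot be derived from the documents. The 38-142 above is an illustration, and larger claims need care. For example, a reader might suppose that 2-3% of 5400 patients (108-162) die a cardiac death by day 30 without earlier HHF, and that these are a quarter of first events. That would imply 432-648 first events by day 30, more than the roughly 402 that the SAP's planning rates give for the full year.

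The 12-month primary analysis and the sample size are not affected.

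**What to change.** Amend the SAP before treatment allocation is joined to the outcome data:

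1. **5.4.1:** limit censoring for death to non-cardiac causes, as in 5.3, with the cut-off at 30 days.
2. **5.4.2 and 5.4.3:** replace the back-references with an explicit statement for each endpoint, at both 30 days and 12 months.
   - Cardiac death alone: among deaths, censor only the non-cardiac ones.
   - All-cause death and MACCE: every death is an event and none is a censoring reason.
   - HHF alone, revascularisation, reinfarction and stroke: censor at death from any cause, and label the hazard ratio as cause-specific.

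The cost is a few sentences in the SAP and matching event and censoring flags in the analysis code. No new data, patients or follow-up are needed, and the sample size does not change.
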